**Table 2: Stopping Boundaries for the Sequential Design.**

| Look # | Sample Size
MT Subjects | Stopping Boundaries (Extended Protocol) |        |                              |        |
|--------|----------------------------|-----------------------------------------|--------|------------------------------|--------|
|        |                            | Efficacy Z
(lower, upper)            |        | Futility Z
(lower, upper) |        |
| 1      | 46                         | 4.333                                   | -4.333 | 0.007                        | -0.007 |
| 2      | 92                         | 2.963                                   | -2.963 | 0.374                        | -0.374 |
| 3      | 138                        | 2.359                                   | -2.359 | 1.261                        | -1.261 |
| 4      | 182                        | 2.014                                   | -2.014 | 2.014                        | -2.014 |

Analysis Plan for Process Evaluation. Most of the process evaluation components (Table 1) naturally render themselves to description and categorization. Noteworthy exceptions are aspects relating to intent-to-treat vs. per-protocol received treatment, and control of head positioning assignment. The data collected will enable generation of statistical quality control charts if necessary, to monitor the proportion of non-conforming patients (delivered treatment different from assigned protocol) over time. Should control charting be necessary, they will be assembled by ZODIAC independent biostatisticians and provided to Drs. [name] and [name] (the study's protocol fidelity and implementation science experts) as an ongoing monitoring effort. The upper and lower control levels of these charts will allow a ready assessment of whether deviations over time or between hospitals are coincidental or driven by some real difference or shift in hospital procedures.

Analysis Plan for Aim 2 (secondary aim assessing safety). Serious adverse events (SAE) that will be monitored closely in this trial include: 1) Severe neurological deterioration; 2) hospital acquired pneumonia; and, 3) death. Analyses will be descriptive and include rates for SAEs by study cohort.

Severe neurological deterioration (SND) is defined as at least a 4-point increase ( $\geq 4$ ) in the NIHSS from the time 0 NIHSS baseline. Our NIHSS serial assessments will allow for early detection of neurologic change in our subjects should it occur. SND is a severe form of deterioration, and consequently, our provision for early trial stopping is a safety measure. Because SND can be due to a number of different factors that may or may not be associated with this protocol, incidents of SND will also be reviewed by the Data Safety Monitoring Board (DSMB) as described below, and adjudicated to the intervention or other factors as indicated by their findings.

Hospital acquired pneumonia (HAP). The American Thoracic Society/Infectious Diseases Society of America (ATS/IDSA) guidelines will be used, defining pneumonia as requiring onset of a new or progressive infiltrate on pulmonary imaging within 72 hours, along with at least two of the following: 1) Fever  $\geq 38^{\circ}$  C; 2) purulent sputum; 3) leukocytosis or leukopenia; and/or, 4) decline in oxygenation. Based on our pilots, we are excluding cases from enrollment that are high risk for pneumonia; because these cases are kept NPO for thrombectomy, this will further reduce aspiration risk. We therefore believe that pneumonias will be rare and because of this, we believe that exposure to unnecessary additional chest imaging would add both increased cost and unnecessary radiation exposure, especially since stroke patients often require repeat neuroimaging. Instead, excellent nursing assessments will serve as triggers to inform the need for additional chest imaging in the case of pulmonary deterioration. Because pneumonia may be due to a number of different unassociated factors, pneumonia events will be DSMB reviewed and adjudicated to the intervention as indicated.

Death. Death occurring during the active protocol phase, throughout hospitalization, or within 3 months from enrollment will be monitored, and incidents adjudicated by the DSMB. Death may be associated with a number of unassociated factors, therefore the DSMB will carefully determine study association.

Other AEs detected will be DSMB reviewed and reported as related or unrelated to study procedures.

All the safety outcome analyses will be executed in the intention-to-treat population. We will use unadjusted Cox proportional-hazards modeling to compare and Kaplan-Meier curves to visualize the rate of severe early neurological deterioration ( $> 4$  NIHSS points change from baseline) in the two groups. The number at risk and censored in each group will be reported in the Kaplan-Meier survival curves every 10 minutes. Overall and enrollment group rates of SND will be reported as frequencies and percentages and compared between groups with Fisher's Exact test. The number needed to harm for SND will be estimated as the inverse of the absolute risk increase (ARI) =  $1/\text{ARI}$ . Rates of hospital-acquired pneumonia, discharge, 90-day participant's death, post-discharge stroke, and symptomatic intracerebral hemorrhage post-reperfusion treatment will be reported in frequencies and percentages; these will be compared between groups using Fisher's Exact test together with odds ratios and the corresponding 95% confidence intervals and p-values from unadjusted logistic regression models that include randomization assignment as the predictor.

Pre-Specified Exploratory Endpoints: As discussed, END is the primary endpoint for this clinical trial and is measured proximally, at the termination of the intervention monitoring period. Our rationale for not utilizing a post-thrombectomy 90-day outcome is twofold: First, head positioning should not be deemed a "treatment" for LVO stroke; instead, head positioning is a rescue procedure similar to other medical care that is utilized to stabilize, optimize, and ensure both patient safety and optimal outcomes. The impact of a rescue procedure such as head positioning is best measured during the time it is implemented to determine its efficacy in supporting and optimizing patient condition. Second, thrombectomy is a highly effective definitive treatment for large vessel occlusion stroke patients. The tremendous effect size of thrombectomy may likely override any benefit of other interventions, including

head positioning, however this remains unknown at this time. In summary, we aim to determine the efficacy of head positioning as a simple rescue procedure, making measurement of END at the time of positioning on the catheterization lab table for thrombectomy (or immediately prior to elective induction/intubation in sites using general anesthesia for thrombectomy) our choice as the study primary endpoint.

That said, we have identified several pre-specified exploratory endpoints that can be used to examine whether any continued benefit from head positioning occurs in combination with thrombectomy treatment. Specifically, the ZODIAC study will examine the following exploratory endpoints for between group differences:

- 24-hour NIHSS scores
- 7 day or discharge (whichever occurs first) NIHSS scores
- 7 day or discharge (whichever occurs first) mRS
- 90-day mRS

We will examine improvement rates at 24 hours and again at discharge/7 days (whichever comes first) in the NIHSS and will report this as frequencies and percentages; these will be compared between groups using Fisher's Exact test together with odds ratios and the corresponding 95% confidence intervals and p-values from unadjusted logistic regression models that include randomization assignment as the predictor. Changes from baseline NIHSS for individual subjects will be plotted by means of a linear plot according to their randomization group to visualize the changes in NIHSS after randomization in each group; a repeated measures ANOVA will be employed to compare the serial NIHSS measures between the two groups. The 90-day mRS will be analyzed in 3 ways: 1) Dichotomized as 0-2/3-6 and 0-3/4-6 and modeled as a dependent variable by unadjusted logistic regression with randomization assignment as the predictor. The 90-day mRS will be plotted using a paired horizontal bar graph (aka "Grotta bars") for visualization; 2) Analyzed as separate categories and modeled by unadjusted ordinal logistic regression as a dependent variable and with randomization assignment as the predictor. The proportional odds assumption will be verified by likelihood ratio testing; and 3) Transformed to a utility-weighted mRS (UW-mRS) where each of the mRS categories (from 0 to 6) is assigned a weight (1.00, 0.91, 0.76, 0.65, 0.33, 0.00 and 0.00) and modeled as a dependent variable by unadjusted linear regression, with randomization assignment as the predictor.

Of note, ZODIAC is not powered for these exploratory analyses, so interpretation of any findings from these analyses must take this into account.

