Aim 1 will be supported by a process evaluation plan that identifies key components (context; reach and recruitment; implementation dose delivered and received; and, overall fidelity), related questions, and associated process stability indicators. Implementation methods are proposed to support, continuously monitor, report, and improve process stability and overall protocol fidelity.

Aim 2 (secondary aim assessing safety): To confirm the safety of 0°-HOB positioning in a large, generalizable sample of hyperacute large artery ischemic stroke patients.

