**Randomization and power/sample size.** Our protocol utilizes two groups, 0°-HOB and 30°-HOB, and allows us to offer enrollment to consecutive eligible patients. To assure balance in the treatment group throughout the course of enrollment, we will use block randomization with a block size of 4 and an allocation ratio of 1:1. This scheme has been implemented in the *Unity* computerized enrollment procedure that only shows the random assignment for a single given participant to the user and may scramble subject enrollment numbers to ensure randomization balance. Future assignments cannot be predicted by study personnel because of the block assignment made together with assignments at all sites, and this effectively mitigates the risk for selection bias that might occur if anticipated group assignment were able to influence enrollment decisions.

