### Endpoints.

Primary Endpoint: The percentage of patients with early neurologic deterioration (END) is our primary outcome. END is defined as a two or more point worsening ( $\geq 2$ ) in the NIHSS score in comparison to the time-0 NIHSS score at the time of positioning intervention termination (placement of the patient on the catheterization table or immediately prior to the time of elective induction/intubation for thrombectomy in centers utilizing general anesthesia). Not deteriorating (being stable) is defined as less than 2-point NIHSS worsening ( $< 2$ ) or NIHSS score improvement in comparison to the time-0 NIHSS score during the head position intervention.

We expect to see at most 5% of END participants in the 0° head position group, compared to 20% of END patients in the 30° head position group (15% lower deterioration). Our group-sequential design allows for early stopping due to futility or efficacy and is based on a two-sample two-sided proportion test as implemented in East 6.0 (Cytel, Cambridge, MA) with type I error  $\alpha=0.05$  and 80% power; it incorporates 3 interim analyses and 1 final look at the data which results in a sample size of  $n = 182$ . Interim analyses are planned with equal spacing after cases have been enrolled/observed for the primary endpoint (Table 2). The Lan-Demets alpha and beta spending approach with O'Brien-Fleming

boundaries are used both for futility and efficacy interim monitoring. Absence of primary endpoint evaluation will be counted as an END event so that all randomized participants will have a determined primary endpoint available for analysis, allowing for an intent-to-treat analysis with no primary endpoint attrition.

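### The planned safety odds and hazard ratios have no fallback for an arm without events, and Aim 2 is to confirm safety without stating a margin

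*Supplement*

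**What the plan says.** All references are to protocol version 2.0 in the supplement.

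- *Specific Aims*, Aim 2: "To confirm the safety of 0°-HOB positioning in a large, generalizable sample of hyperacute large artery ischemic stroke patients".
- *Analysis Plan for Aim 2*, opening paragraph: "Analyses will be descriptive and include rates for SAEs by study cohort".
- Same section, hospital-acquired pneumonia: "We therefore believe that pneumonias will be rare". No rate is given. No other safety outcome is called rare.
- Same section, after the paragraphs on individual events: severe neurological deterioration (SND) is compared by an unadjusted Cox model and Fisher's exact test. Pneumonia, death, post-discharge stroke and symptomatic intracerebral haemorrhage are reported as frequencies and percentages, and compared by Fisher's exact test and, beside it, "odds ratios and the corresponding 95% confidence intervals and p-values from unadjusted logistic regression models that include randomization assignment as the predictor".
- No exact, penalised or other sparse-data estimate is named for the odds or hazard ratio. No safety margin, acceptable excess or safety power is stated. The caveat about lack of power, under *Pre-Specified Exploratory Endpoints*, covers the exploratory analyses only.

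**The concern.** An unadjusted logistic model with one binary predictor is a two-by-two table. If one arm has no events, the likelihood keeps rising as the log odds ratio runs off to infinity. Software then prints either a failure or a huge coefficient with a huge standard error, a Wald interval that covers everything and a Wald p-value near 1. The Cox model behaves in the same way. The plan foresees few pneumonias, so it should say what happens then.

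The plan also attaches two p-values to each of these outcomes without saying which governs, and they can fall on opposite sides of 0.05.

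Finally, three statements pull apart: the aim is to confirm safety, the analysis is called descriptive, and the same section goes on to test. For a safety aim the most useful output is a bound on the excess risk in the 0° arm. Fisher's p-value gives no such bound, and the ratio with its interval is the part that fails.

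**Working it through.** **Inputs.** Total 182 (*Endpoints*); "block size of 4 and an allocation ratio of 1:1" (*Randomization and power/sample size*), hence about 91 per arm. Look 2 is at 92 patients (Table 2), about 46 per arm. Expected early neurologic deterioration (END) in the 0° arm is at most 5% (*Endpoints*). The documents give no safety event rate, so every rate r below is an assumption. They give no safety calculation to reproduce.

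**1. Chance of an empty arm.** With the same true rate r in both arms and n per arm, P(a given arm has no events) = (1−r)^n, and P(at least one empty arm) = 1 − [1 − (1−r)^n]².

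Example, r = 1%, n = 91: 0.99^91 = 0.401; 1 − 0.599² = 0.64.

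| Assumed r | One given arm empty, n = 91 | At least one empty, n = 91 | At least one empty, n = 46 |
|---|---|---|---|
| 1% | 40% | 64% | 86% |
| 2% | 16% | 29% | 63% |
| 3% | 6% | 12% | 43% |
| 5% | 1% | 2% | 18% |

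The last column applies only if the trial stops at look 2. The figures include trials with no event in either arm: 0.401² = 16 points at r = 1%, n = 91, and 0.159² = 2.5 points at r = 2%.

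**2. SND.** Measured at the same time point, SND (a rise of at least 4 points) is contained in END (a rise of at least 2), so the expected 5% would cap it in the 0° arm. The second column then gives the chance of no SND in that arm: 40% at 1%, 16% at 2%, 1% at 5%. The cap is an inference. SND is followed through the serial assessments, whereas END is read at the end of positioning and also counts missing evaluations as events.

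**3. What the planned models return for 0/91 vs 3/91.**

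- Logistic regression does not converge: log odds ratio about −28, standard error about 8×10⁵, Wald p about 1.0.
- Cox, with simulated event times: log hazard ratio about −24.5, standard error about 1×10⁵.
- Fisher's exact p = 0.25, which is valid.
- Exact conditional odds ratio 0 (95% CI 0 to 2.40).
- Adding 0.5 to each cell, which is the Firth estimate for this table: (0.5/91.5)/(3.5/88.5) = 0.14; SE = √(1/0.5 + 1/91.5 + 1/3.5 + 1/88.5) = 1.52; 95% CI 0.007 to 2.71.
- Newcombe risk difference: Wilson limits are 0 to 4.05% for 0/91 and 1.13 to 9.25% for 3/91. The difference is −3.3 points. Lower limit: −3.30 − √[0² + (9.25−3.30)²] = −9.2. Upper limit: −3.30 + √[4.05² + (3.30−1.13)²] = +1.3.

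**4. Disagreement of the two p-values.**

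- 0/91 vs 6/91: Fisher p = 0.029, logistic Wald p = 0.999.
- No empty cell, 2/91 vs 9/91: log OR = ln[(2/89)/(9/82)] = −1.586; SE = √(1/2 + 1/89 + 1/9 + 1/82) = 0.797; z = −1.99; Wald p = 0.046, Fisher p = 0.058.

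**5. What 91 per arm can say about safety.** The exact two-sided 95% upper limit for 0/91 is 1 − 0.025^(1/91) = 0.0397, or 4.0%. Power of Fisher's test at two-sided 0.05, by enumeration, is 3.5% for 2% vs 4%, 14% for 2% vs 6% and 17% for 5% vs 10%.

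**The case against.** Four points on the other side have force.

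- **Fisher's test and raw percentages are planned for every one of these outcomes.** Both are valid with an empty arm. A reader might infer that the whole safety comparison would collapse; it would not.
- **Only pneumonia is called rare.** A reader might extend that to death, symptomatic haemorrhage and SND. Nothing in the documents puts those at 1 to 2%, and at a 5% rate the chance of an empty arm is only 2%. For SND the argument rests on the END figure and its limits above.
- **The plan does not say the limits are Wald limits.** A profile-likelihood interval would have one finite limit with a single empty arm. That softens the point but does not supply a point estimate, and the plan names no such method. With both arms empty no ratio is informative, exact or penalised included; a risk difference still is (Newcombe: 0, ±4.05 points).
- **A reader might infer that a non-significant test is to be taken as proof of safety.** No section says so. The analyses are called descriptive, and the data safety monitoring board adjudicates individual events and can stop the trial for harm. Low power for secondary safety events is also usual in a trial sized for its primary endpoint.

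What remains is that no fallback is named for the effect estimate, no p-value is designated, and *confirm* has no margin behind it. Adjudication attributes single events; it does not estimate the excess between arms.

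**Conclusion.** The concern holds for the effect estimates, not for the whole safety analysis. If an arm has no events, the planned odds ratio (or the hazard ratio for SND), its Wald interval and the model p-value are unusable. For pneumonia this is plausible: 64%, 29%, 12% and 2% at assumed true rates of 1%, 2%, 3% and 5% with 91 per arm, and more after an early stop. For SND in the 0° arm it is possible if the rate is well below 5%. For the other outcomes it is not shown.

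Separately, the wording of Aim 2 claims more than the design can give. No acceptable excess is stated, and even no events among 91 patients is compatible with a true rate of 4.0%. The descriptive label and the planned tests in *Analysis Plan for Aim 2* are in tension. All this concerns the secondary aim and leaves the primary analysis untouched.

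**What to change.** In *Analysis Plan for Aim 2*:

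1. For SND, pneumonia, death, post-discharge stroke and symptomatic intracerebral haemorrhage, report the risk difference (0° minus 30°) with a Miettinen-Nurminen or Newcombe 95% interval. It is defined with one or both arms empty, and its upper limit bounds the excess risk at 0°.
2. If a ratio is wanted, use Firth-penalised logistic and Cox models, or exact conditional odds ratios, in place of ordinary maximum likelihood.
3. Keep Fisher's exact p-value as the only one for each outcome.
4. Reconcile the descriptive label with the tests: either drop the p-values or say that they are reported without a decision rule.

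In *Specific Aims*, change Aim 2 from confirming to estimating safety, and rest the conclusion on the upper limit of the excess risk.

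The cost is plan wording and standard software, with no extra patients or data. The downside is a more modest safety statement.

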We selected individual randomization as opposed to cluster randomization on the hospital/site level for three reasons. First, as emphasized by Murray, “the single most important factor in the power of a group-randomized trial is usually the number of groups.” Had we chosen cluster randomization, our sample size would need to increase from  $n=182$ , to  $n=5800$ , and this would demand at least 29 study sites to efficiently complete the study within 5 years. Given that the largest individually randomized thrombectomy trial included a maximum of 500 patients, and took over 3 years to complete at 16 sites, the conduct of a cluster randomized trial with an even larger thrombectomy sample would require considerable manpower and monetary support, much greater than can be provided. In addition, our 12 geographically widespread sites contribute diverse patients while delivering a consistent standard of care strictly managed by national guidelines, stroke center certification, and core measure requirements. Subject diversity is problematic in a cluster randomized design due to an inability to balance important patient traits. In trials involving a small number of clusters ( $\leq 10$  pairs), the loss of degrees of freedom resulting from pair matching becomes a particularly critical factor. Detailed investigation of this problem has led to the conclusion that for studies with a small number of clusters it is unlikely that effective matching can be possible and that “matching may be overused as a design tool.” In contrast, our use of individual (block) randomization will effectively balance patient traits and tPA treatment across protocols, considerably strengthening the evidence derived from this trial. Furthermore, if randomization would be determined on the hospital level, the attending physicians and nurses would know the protocol that would be applied to a patient before that patient is asked to give informed consent. Thus, group-randomization would open our study to enrollment selection bias due to differentially approaching patients that are deemed more/less likely to benefit from the pre-determined protocol for each hospital. This may, in fact, have contributed to enrollment of only small vessel strokes in HeadPoST. Group randomization would also challenge NIHSS/mRS score blinding. In summary,

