Analysis Plan for Aim 1 (primary efficacy endpoint); Hypothesis: *Patients with large artery occlusions placed in a 0°-HOB position will experience less early neurological deterioration than those in the 30°-HOB elevation group.* We will apply sequential testing in both patient groups (Table 2). As an example, the first look in the protocol is performed when 46 participants are enrolled/have their primary outcome evaluated; if the z-value associated with the test of equality of proportions in both arms is above 4.333 or below -4.333 the trial will be stopped early for efficacy (one group is clearly superior with respect to the primary outcome), whereas if that z-value is in the interval (-0.007, 0.007), the trial will be stopped early for futility (groups are essentially identical in outcome). If the z-value falls within the intervals (-4.333, -0.007) or (0.007, 4.333), the trial will continue until the next look at the data. Note that for the primary endpoint, absence of evaluation is counted as deterioration and that, consequently, all randomized participants will have a determined primary endpoint available for the analysis; therefore, intent-to-treat principles will support our primary data analysis. We will use unadjusted Cox proportional-hazards modeling to compare and Kaplan-Meier curves to visualize the rate of early neurological deterioration (> 2 NIHSS points change from baseline) in the two groups. The number at risk and censored in each group will be reported in the Kaplan-Meier survival curves every 10 minutes. Overall rates of END and according to group will be reported as frequencies and percentages and compared between groups with Fisher's Exact test. The number needed to harm will be estimated as the inverse of the absolute risk increase (ARI) = 1/ARI.

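### The exploratory NIHSS and mRS regressions are all unadjusted although time-0 NIHSS is measured in every subject; the analyses are valid but give up precision and power

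*Supplement*

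**What the plan says.** All references are to protocol version 2.0.

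- **Exploratory endpoints.** Under Pre-Specified Exploratory Endpoints, NIHSS improvement at 24 hours and at 7 days/discharge is compared by Fisher's exact test and unadjusted logistic regression. The 90-day mRS is analysed by unadjusted logistic regression at two cut-points, by an ordinal model ("Analyzed as separate categories and modeled by unadjusted ordinal logistic regression as a dependent variable and with randomization assignment as the predictor") and, as utility-weighted mRS (UW-mRS), by unadjusted linear regression. A repeated measures ANOVA of serial NIHSS is also planned, with nothing said about covariates. The section states that the trial is not powered for these analyses.
- **END and safety.** For END, the Analysis Plan for Aim 1 says "We will use unadjusted Cox proportional-hazards modeling to compare". The severe-deterioration Cox model and the logistic models for safety events are likewise unadjusted.
- **Primary decision.** The sequential decision on END is a "two-sample two-sided proportion test as implemented in East 6.0", not a regression.
- **Randomization.** The plan says "we will use block randomization with a block size of 4 and an allocation ratio of 1:1", with "block assignment made together with assignments at all sites". No stratification factor is named. In arguing against cluster randomization, the same section says "our use of individual (block) randomization will effectively balance patient traits and tPA treatment across protocols".
- **Baseline data.** Under Enrollment and Serial Monitoring, a protocol-naïve rater scores the time-0 NIHSS in all subjects while they are flat, before the assigned position is taken up.

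**The concern.** Starting severity is an obvious candidate predictor of later NIHSS and 90-day mRS, and the trial holds it for everyone. A model with arm alone leaves the variation due to severity in the error term. The plan already concedes that these endpoints are underpowered, which is a reason to use a baseline value in hand. Version 2.0 also admits patients up to 24 hours from onset, which may add prognostic spread that no model takes up.

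Blocks of four run across all sites balance the number of patients per arm. They do not balance severity, tPA use or site except on average. The statement about tPA balance therefore promises more than the scheme delivers, and no planned analysis shows how far a chance imbalance matters. At stake is the sharpness of the exploratory results, not the primary conclusion.

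**Working it through.** **1. The plan's own figures.** The plan states: "We expect to see at most 5% of END participants in the 0° head position group, compared to 20% of END patients" in the 30° group, with two-sided α 0.05, 80% power, four looks and n = 182, or 91 per arm. A fixed design with pooled variance needs 76 per arm, 152 in all. Simulating the Table 2 boundaries gives an inflation factor of about 1.08, hence about 156–165 without continuity correction and 190 with it. Power at 182 is 83.5–85.6% without the correction. The exact 182 is not reproduced, but the stated 80% is met on that basis, and none of this bears on the present point. What is needed below is 91 per arm and the expected END count: 91 × (0.05 + 0.20) = 22.75, about 23 events.

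**2. Linear UW-mRS model.** The documents give no R², so 0.10–0.30 is an assumption. Adjustment multiplies the variance of the arm effect by about 1 − R². Effective sample size is 182/(1 − R²), and the interval narrows by 1 − √(1 − R²).

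| Assumed R² | Effective N | Interval narrower by |
|---|---|---|
| 0.10 | 182/0.90 = 202 | 5% |
| 0.15 | 182/0.85 = 214 | 8% |
| 0.20 | 182/0.80 = 228 | 11% |
| 0.30 | 182/0.70 = 260 | 16% |

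**3. Ordinal mRS model.** The variance formula does not carry over, so power was simulated: n = 182, odds ratio 2.0 given covariates, 400 runs per row. Monte Carlo error of a single power figure near 70% is √(0.7 × 0.3/400), about 2.3 points; both models were fitted to the same data sets.

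| Latent R² (assumed) | Ordinal power, unadjusted → adjusted | UW-mRS power, unadjusted → adjusted | UW-mRS SE ratio |
|---|---|---|---|
| 0.07 (weak) | 68% → 73% | 66% → 70% | 0.97 |
| 0.23 (moderate) | 66% → 75% | 61% → 68% | 0.89 |
| 0.41 (very strong) | 49% → 73% | 43% → 62% | 0.80 |

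For weak to moderate covariates the ordinal gain is about 5–9 points. The SE ratios agree with step 2: 0.89² ≈ 0.80, which corresponds to an R² of about 0.20. Gains for the dichotomized mRS and NIHSS-improvement models were not quantified separately.

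**4. END.** A logistic model with about 23 events and four covariates, 1,000 runs: power 89% → 90% (weak covariates) and 87% → 90% (strong). The gain of 1–3 points is within, or close to, simulation error.

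**5. tPA balance.** tPA use is not given; 30–60% is assumed. At 50% use, the SD of the arm difference is √(2 × 0.5 × 0.5/91) = 0.074. A difference of at least 10 points needs at least 10 patients, since 9/91 is 9.9%, so exact counting is used. The chance of such a difference is:

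| tPA use | Independent binomials | Hypergeometric (total fixed) |
|---|---|---|
| 30% | 12.4% | 10.6% |
| 40% or 60% | 15.0% | 13.0% |
| 50% | 15.9% | 13.8% |

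The range is about 11–16%.

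**The case against.** The strongest reply is that nothing here is wrong. An unadjusted comparison in a randomized trial is valid, and its nominal interval already allows for chance imbalance. The primary decision rests on the Table 2 z-test. The endpoints concerned are labelled exploratory and not powered. All of that stands and limits the point to efficiency.

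Several stronger readings are tempting, and the documents do not support them:

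- **Every interval is too wide.** Adjustment narrows the interval only in the linear model, and UW-mRS is the only linear regression planned. In logistic, ordinal and Cox models it generally does not narrow the interval on the log scale. Power rises because the conditional effect is larger, so the estimand changes too.
- **Baseline severity is ignored.** It is partly used: END and severe deterioration are defined as change from time 0, and NIHSS improvement is analysed.
- **The plan guarantees tPA balance.** It claims effective balance, in a passage contrasting individual with cluster randomization, where the contrast is fair.
- **The plan itself names tPA imbalance as a confounder.** The note under Exclusion Criteria concerns thrombolysis more than 15 minutes before randomization and deals with it at enrollment. It does not speak of differences between arms.
- **All covariates are in hand.** Only time-0 NIHSS is clearly measured in everyone. Age and tPA as data fields are inferred, tPA is not stated always to precede randomization, and pre-stroke mRS is restricted to 0–1, so it can explain little.

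**Conclusion.** The point holds as one of efficiency in exploratory endpoints. Under an assumed R² of 0.10–0.30, omitting baseline covariates costs the UW-mRS analysis the equivalent of about 20–78 patients (202 − 182 to 260 − 182), with intervals that could be about 5–16% narrower. Under the simulated scenarios it costs the ordinal mRS model about 5–9 points of power; a gain of 24 points appears only with very strong covariates and should not be expected. These sizes rest on prognostic strengths that the documents do not give.

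The balance statement is true only in expectation. A tPA difference of 10 points or more has a chance of about 11–16% at 91 per arm if tPA use is 30–60%.

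A reader might infer that the head-position effect is biased or that the END conclusion is weakened. Neither follows: the unadjusted analyses are valid, the z-test is untouched, and with about 23 expected END events adjustment would add almost nothing there.

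**What to change.** 1. Under Pre-Specified Exploratory Endpoints, specify the 90-day mRS models (dichotomized, ordinal, UW-mRS) and the NIHSS-improvement models with arm plus time-0 NIHSS. Where recorded at baseline, add age, tPA given before randomization, and onset window (up to 6 hours versus over 6 hours).
2. Report the unadjusted result alongside, and state that the adjusted odds ratios are conditional effects.
3. Leave the Table 2 z-test, the END and severe-deterioration Cox models and the sparse safety models unadjusted.
4. Under Randomization and power/sample size, say that tPA treatment and patient traits are balanced in expectation, and report tPA by arm.

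The cost is a change of wording, a little more analysis work and a conditional estimand in the non-linear models. No new data are needed for time-0 NIHSS, and the sequential test does not change. The Summary of Research Protocol Changes records that enrollment closed on 11/01/23, so stratification can no longer be added. If outcomes by arm have already been seen, the adjusted models should be labelled post hoc.
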